## Abstract

**Background:**

Endoscopic retrograde cholangiopancreatography (ERCP) is a gastrointestinal procedure that requires a relatively motionless patient during the intervention. Deep sedation by intravenous propofol combined with an opioid has recently become the preferred sedation technique. However, when high doses of propofol are used, side effects, namely respiratory depression, may occur. Esketamine has hypnotic, analgesic, and sympathomimetic effects. Our assumption is that a combination of propofol with esketamine reduces the dosage of individual drugs, thereby minimizing sedation side effects while keeping the same satisfaction level of patients and endoscopists.

**Methods/design:**

The study will be performed as a randomized controlled multicenter trial. Patients undergoing ERCP, ≥ 18 years old, with American Society of Anesthesiologists (ASA) classification I–III will be randomized after written informed consent to group K (propofol/esketamine) or to group A (propofol/alfentanil). The primary outcome, reflecting effectiveness of sedation, is the total dose of propofol. Secondary outcome parameters are patients’ and endoscopists’ satisfaction with the procedure and the number of sedation-related pulmonary and cardiovascular events. Data on sedation-related events are collected by recording of oxygen saturation (SpO_2_), respiratory rate (RR), end-tidal CO_2_ (etCO_2_), heart rate (HR), arrhythmias (electrocardiogram (ECG)), and non-invasive blood pressure (NIBP) measurements. Satisfaction parameters are collected by means of questionnaires before and after the procedure and on the following day.

**Discussion:**

Esketamine is known for its effective anesthetic and analgesic effects maintaining spontaneous breathing and airway reflexes. Due to an increase in sympathetic tone, hypotension and cardiac depression is less common. Unfortunately esketamine is also known for its psychotomimetic effects. We aim to demonstrate that the combination of esketamine with propofol for sedation in patients subjected to ERCP interventions is nevertheless superior to a combination of propofol with an opioid.

**Trial registration:**

Nederland’s Trial Register, NTR5486. Registered on 17 September 2015.

**Electronic supplementary material:**

The online version of this article (doi:10.1186/s13063-017-2197-8) contains supplementary material, which is available to authorized users.

## Background

Endoscopic retrograde cholangiopancreatography (ERCP) is a complicated, often painful gastrointestinal procedure. It is used for diagnostic purposes in biliary and pancreatic disease and also for therapeutic interventions such as sphincterotomy, gallstone extraction, and biliary and pancreatic duct stenting. Because any movement of the patient could importantly affect success of the ERCP, procedures are usually performed under deep sedation or even general anesthesia with the patients in the semi-prone or prone position [1–3]. Over the last decade the combination of propofol and an opioid has become the preferred sedative regime during ERCP in many countries, despite known side effects.

Esketamine, the s-enantiomer of ketamine - is not only a well-known sedative, but also has strong analgesic properties. Furthermore, its sympathomimetic qualities can counteract the hemodynamic depression of propofol and so reduce the risk of cardiovascular and respiratory depression during sedation. A potential problem of esketamine could be its psychotomimetic effects, such as visual disturbances, vertigo, or nausea that could compromise patient satisfaction. There is still little evidence of an improved safety profile of a combination of propofol/esketamine and it is still open to discussion whether esketamine psychomimetic effects play a significant role in outpatient treatment.

## Methods/design

### Aim of the study

We hypothesize that procedural sedation with propofol and esketamine reduces the dosage of individual drugs, thereby minimizing sedation side effects while keeping the same satisfaction level of patients and endoscopists. To test this hypothesis we compare two groups. Group K receives propofol/esketamine sedation; group A receives propofol/alfentanil sedation during ERCP. Both groups receive standard deep sedation with propofol target controlled infusion (TCI) provided by specialized sedation anesthesia nurses.

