### Secondary objectives

#### Definition of secondary endpoints

Secondary endpoints focus on the satisfaction of patients and endoscopists with sedation and side effects, and on hemodynamic stability and safety, which is reflected in the number of respiratory and cardiovascular events.

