### Statistical analysis

Statistical analyses will be performed using SPSS statistics. All data will be checked for normal distribution using the Kolmogorov test. For normally distributed data, continuous variables will be analyzed using the independent Student’s *t* test and the variables will be presented as mean ± standard deviation (SD). Non-normally distributed data will be compared using the Mann-Whitney *U* test where appropriate, and data will be presented as the median and interquartile range (IQR). For categorical variables, cross-tabulation and the Pearson chi-squared test will be applied and variables will be allegorized as number and/or percentage of the total. To compare the continuous measurements of HR, NIPD, and SpO_2_ between the groups, the area under the curve (AUC) for each value will be calculated over the different measurement time points during the procedure. A *p* value <0.05 will be considered statistically significant. Confidence intervals will be reported where appropriate.

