The most widespread doubts about esketamine, however, correspond to its mind-altering effects in cognition. It can produce psychotomimetic effects that may be associated with symptoms similar to dissociative states of mind [14]. On the other hand, Nakao et al. [15] showed that propofol used in clinical relevant dosages suppresses these effects via the activation of GABA receptors. Unfortunately, there are only a few studies with only limited significance investigating the effectiveness of a propofol/esketamine regime with emphasis on the aforementioned safety aspects during ERCP and the eventually psychotomimetic effects such as visual disturbances, vertigo, or nausea that could compromise patient satisfaction and recovery after discharge home.

A limitation of our study could be that we based sample size calculation on the reduction of the total dosage of propofol. Probably, acute respiratory or hemodynamic adverse events would have been a more appropriate primary outcome. However, much larger-scale studies would have been necessary to address this outcome. Alongside this we defined cardiorespiratory events according to the SIVA consensus statement for standardized definitions and terminology for sedation-related adverse events. However, their clinical impact cannot be determined when a sedation specialist provides adequate rescue maneuvers during such events.

The aim of our trial is to show that the synergy of esketamine and propofol reduces the dosage of individual drugs, thereby providing a better safety and satisfaction profile than the combination with an opioid during ERCP.

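### Satisfaction is hypothesized to stay the same in one place and aimed to be better in another, and the planned difference tests cannot confirm that it is the same

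*Protocol article*

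**What the plan says.** The Aim of the study section hypothesizes that propofol with esketamine lowers the doses of the individual drugs, "thereby minimizing sedation side effects while keeping the same satisfaction level of patients and endoscopists", and states that the two groups are compared in order to test this. The Background of the Abstract uses the same words, there as an assumption.

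The last paragraph of the main Discussion gives the aim as lower doses, "thereby providing a better safety and satisfaction profile than the combination with an opioid during ERCP".

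The Discussion part of the Abstract says the esketamine combination "is nevertheless superior to a combination of propofol with an opioid", without naming an outcome.

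Satisfaction is secondary: "Secondary endpoints focus on the satisfaction of patients and endoscopists with sedation and side effects". The sample size under Number of patients needed rests on propofol dose alone.

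Under Statistical analysis, normally distributed continuous data go to an independent *t* test and non-normal data to the Mann-Whitney *U* test. For categorical data, "cross-tabulation and the Pearson chi-squared test will be applied". The only decision rule is that a *p* "value <0.05 will be considered statistically significant". Confidence intervals are promised where appropriate, without a link to satisfaction or to a margin.

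**The concern.** Keeping satisfaction at the same level is a claim of equivalence, or at least of no relevant loss. A better satisfaction profile is a claim of superiority. They need different inference, and a reader cannot tell which one the trial intends to make.

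The listed tests ask only whether the arms differ. A significant result can support *better* or *worse*. A non-significant result supports neither *better* nor *same*: it is what one expects when there is no difference, and also, often, when there is a moderate difference that the trial is too small to detect.

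This bears on the trial's own argument. The Background and the Discussion both name psychotomimetic effects as something that could compromise patient satisfaction. Less propofol without a loss of satisfaction is the trade-off on which the case for esketamine rests, and the stated tests cannot establish its second half.

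**Working it through.** **Inputs.** From Number of patients needed: mean propofol dose 580 mg, SD 190 mg, a reduction of about 15%, power 0.80, type I error 0.05, 76 per arm, 83 per arm randomized. The article gives no SD, scale or margin for satisfaction. The satisfaction figures are therefore in SD units, over a range, and assume a roughly continuous score.

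**1. The plan's own figure.** The target difference is 0.15 × 580 = 87 mg, or 87/190 = 0.458 SD. With n = 2(1.96 + 0.842)²/0.458², the normal approximation gives 75 per arm and the *t*-based solution gives 75.84, rounded up to 76. A one-sided test would need only 59, so the calculation is two-sided. The stated 76 reproduces, for propofol dose only.

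**2. How often a true loss in satisfaction would be non-significant.** The standard error of a mean difference in SD units is √(2/76) = 0.162. Approximate power is Φ(d/0.162 − 1.96); the *t*-based values are shown beside it.

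| True loss | Power, *t* test | Non-significant, *t* test | Non-significant, normal approximation |
|---|---|---|---|
| 0.2 SD | 0.232 | 77% | 77% |
| 0.3 SD | 0.451 | 55% | 54% |
| 0.4 SD | 0.688 | 31% | 31% |

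If all 83 randomized patients per arm were analyzed, the normal approximation gives 75%, 51% and 27%.

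**3. What a confidence interval could show.** The 95% half-width is 1.976 × 0.162 = 0.32 SD.

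**4. What a non-inferiority claim would need.** With one-sided 0.025, 80% power and no true difference, the smallest workable margin is (1.96 + 0.842) × 0.162 = 0.45 SD with 76 per arm, or 0.43 SD with 83. Patients needed per arm, from n = 2(1.96 + 0.842)²/m²:

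| Margin m | Per arm |
|---|---|
| 0.2 SD | 393 |
| 0.3 SD | 175 |
| 0.4 SD | 99 |
| 0.5 SD | 63 |

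**5. What a wide margin lets through.** With 76 per arm and a 0.5 SD margin, a true loss of d passes with probability Φ((0.5 − d)/0.162 − 1.96). This is about 46% for d = 0.2 SD and 23% for d = 0.3 SD. The margin therefore has to be justified clinically, and not chosen because the sample can support it.

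**The case against.** Several points on the other side are sound.

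- A reader might infer that the investigators will report a non-significant result as maintained satisfaction. The article does not say so. It sets a threshold for significance, gives no rule for results above it, and promises confidence intervals where appropriate. The misreading is a risk, not a stated plan.
- A reader might take the Abstract's Discussion as claiming superior satisfaction. It names no outcome for its superiority claim. The conflict lies between the hypothesis (Abstract Background and Aim of the study) and the final paragraph of the main Discussion.
- A missing margin for a secondary endpoint is not a fault in itself. The full protocol and any statistical analysis plan are not shown, and such detail is commonly left to them.
- The SD-unit figures depend on a scale the article does not give. Under Questionnaires, overall patient satisfaction and the endoscopists' satisfaction item have no stated scale, and the question on recommending the sedation regime is categorical. Some items may be analyzed by Mann-Whitney or chi-squared, for which the percentages are only indicative.
- Non-inferiority is not the only remedy. Rewording the hypothesis costs less and needs no margin.

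These points narrow the concern but do not remove it. *Same* and *better* are both stated as aims in this document, and no unseen analysis plan reconciles two stated aims. The mismatch between a hypothesis of sameness and a list of difference tests is also in the text as it stands.

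**Conclusion.** The point holds as an inconsistency in the stated aims, together with a stated analysis that cannot confirm one of them. Its size is conditional: if p≥0.05 were taken as support for *same*, true losses of 0.2 to 0.4 SD would go unflagged in about 77% to 31% of trials. That assumes 76 analyzed per arm, a two-sided 0.05 test and a roughly continuous score.

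A reader might go further and hold that the trial must be recast as a non-inferiority trial for satisfaction, or that its main conclusion is at risk. The documents support neither. Satisfaction is secondary, and the propofol-dose endpoint, its test and its sample size are untouched. This is a moderate issue.

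**What to change.** State one direction for satisfaction in the Abstract Background, the Aim of the study and the closing paragraph of the Discussion. Report the between-group difference in patient and in endoscopist satisfaction with its 95% confidence interval, and state that p≥0.05 will not be taken as evidence of equality.

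Then choose one course:

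- **If *same* or *not worse* stays as a claim:** set a clinically justified margin before unblinding, and make the claim only if the confidence interval excludes a loss beyond it. If a margin of about 0.45 SD is too wide to be acceptable, drop the claim and report the estimate with its interval.
- **If *better* is the aim:** reword the hypothesis to match. The listed difference tests then fit it.

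The cost is wording and, for the first course, agreement on a margin. No extra patients are needed unless the sponsor wants 80% power for a margin narrower than about 0.45 SD. The downside is that maintained satisfaction becomes harder to claim.

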### Trial design

The study is designed as a prospective, randomized, controlled, multicenter trial and reported following the Standard Protocol Items: Recommendations for Interventional Trials (SPIRIT) statement [4]. The sponsor of this trial is the Department of Anesthesiology of the Academic Medical Center (AMC) in Amsterdam. The sponsor is responsible for the collection, management, analysis, and interpretation of data; writing of the report; and the decision to submit the report for publication. The study is supported by institutional funding. Additional file 1 shows the SPIRIT checklist that we followed in this report.

### Participants

#### Number of patients needed

Alfentanil reduces the required hypnotic dose of propofol by 20–50% at fairly low doses according to the literature [5]. A 15% reduction in propofol requirement when using esketamine instead of alfentanil would reflect a total dose reduction of propofol by up to 65%, which is not only a statistically significant but also a clinically relevant difference.

The sample size calculation is based on retrospectively obtained observational data from previous ERCPs, collected in our hospital sedation database. The primary endpoint is the difference in the dose of propofol used. The mean dosage of propofol during ERCP was 580 mg, with a standard deviation of 190 mg. We will need to study 76 subjects in each group, given power of 0.80 and type I error of 0.05, to reduce propofol requirement by about 15%. Considering a dropout rate of 10%, the estimated sample size will be 83 patients per group, thus a total of 166 patients will be randomized.

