#### Consent

Patients’ medical history and their current state of health are screened on paper during standard anesthetic pre-assessment before the scheduled sedation. The investigator uses the anesthetic pre-assessment form to screen patients for inclusion and exclusion criteria. Patients meeting inclusion criteria are contacted by phone to verify criteria and asked for their willingness to participate in this study. Further information is sent by mail if they agree to participate. Final inclusion occurs after written informed consent is provided on the day of the procedure.

If patients decline to take part in the study, they are sedated according to the AMC standards with propofol and alfentanil. The investigator or physician performing the examination can decide to withdraw a subject from the study for urgent medical reasons (allergic reactions or acute health problems).

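### The 65% total propofol reduction adds percentages taken on different bases; the stated inputs give at most 57.5%, and the sample size is unaffected (minor correction)

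*Protocol article*

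**What the plan says.** All the figures are in the protocol article under Number of patients needed.

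- Alfentanil's effect, from the literature: "Alfentanil reduces the required hypnotic dose of propofol by 20–50% at fairly low doses".
- The target: "A 15% reduction in propofol requirement when using esketamine instead of alfentanil" "would reflect a total dose reduction of propofol by up to 65" per cent. The article then calls this difference clinically relevant.
- The planning data, from the hospital's sedation database: "The mean dosage of propofol during ERCP was 580 mg, with a standard deviation of 190 mg". The regimen used in those procedures is not named.
- The evaluable sample: "We will need to study 76 subjects in each group, given power of 0.80 and type I error of 0.05", for a reduction of about 15%.
- The allowance for loss: "Considering a dropout rate of 10%, the estimated sample size will be 83 patients per group, thus a total of 166 patients will be randomized".

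The Consent section gives the only hint about the database regimen. Patients who decline the study receive routine care: "they are sedated according to the AMC standards with propofol and alfentanil".

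**The concern.** The only route from the stated inputs to 65 is 50 + 15, and those two percentages have different denominators. The first is a share of the propofol dose needed without alfentanil. The second, as worded, is a share of the dose needed with alfentanil. They cannot be added.

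The total is offered in support of calling a 15% difference clinically relevant. The primary endpoint is a drug dose, and the Discussion concedes that adverse events would probably have been a more appropriate primary outcome. The relevance argument for the dose difference should therefore rest on correct figures.

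The dropout sentence in the same paragraph has a smaller flaw. Inflating 76 for 10% loss does not give 83.

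**Working it through.** **1. The plan's own sample size.** Inputs: mean 580 mg, SD 190 mg, reduction 15%, power 0.80, alpha 0.05. Sidedness is not stated; two-sided is assumed here.

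- Difference: 0.15 × 580 = 87 mg. Standardized effect: 87/190 = 0.458.
- Normal approximation: 2 × (1.960 + 0.842)² × (190/87)² = 74.87, so 75 per group.
- Two-sample t test (noncentral t): 75.84, so 76 per group, as stated.
- A one-sided t test would give 59.7, so 60. The two-sided assumption is the one that matches.

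**2. The combined reduction.** Let *a* be alfentanil's effect against propofol alone (0.20 to 0.50), followed by a further 15% relative to the alfentanil regimen. The total is 1 − (1 − *a*) × (1 − 0.15).

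| *a* | Total reduction against propofol alone |
|---|---|
| 0.20 | 1 − 0.80 × 0.85 = 32% |
| 0.50 | 1 − 0.50 × 0.85 = 57.5% |

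The stated maximum of 65% exceeds 57.5% by 7.5 percentage points.

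**3. The percentage-point reading.** Suppose instead that 15 points of the propofol-alone dose were meant. The reduction against alfentanil would then be 0.15/0.80 = 18.75% at the low end and 0.15/0.50 = 30% at the end where the total is 65%. If 580 mg is the alfentanil-regimen mean, 30% is 174 mg, the standardized effect is 174/190 = 0.916, and about 20 per group would suffice. That does not match the 76 in the plan. If 580 mg were a propofol-alone mean, 87 mg would be 15 points of it and the 65% would be coherent, but the 15% could not then be relative to alfentanil.

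**4. The dropout allowance.**

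- Needed for 76 evaluable after 10% loss: 76/0.90 = 84.4, so 85 per group (170 in total).
- The stated 83 looks like 76 × 1.1 = 83.6 rounded down.
- Evaluable after 10% loss from 83: 83 × 0.90 = 74.7.
- Loss that still leaves 76: 1 − 76/83 = 8.4%.
- Power for 87 mg with the t test: 0.801 at 76, 0.794 at 74.7 and 0.790 at 74 per group. By normal approximation it is 0.799 at 74.7.
- Difference detectable with 80% power at 74.7 per group: 87 × √(75.84/74.7) = 87.7 mg, or 15.1% of 580 mg.

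**The case against.** The strongest reply is that nothing depends on the 65%. It is a hedged upper bound built on a wide literature range, it enters no calculation, and a maximum of 57.5% would carry much the same argument. This stands, and it makes the point a correction to the rationale only. A phrase that gives a maximum also need not report the low end, so leaving out 32% is no error.

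A second reply is that the article never says which regimen produced the 580 mg. This stands too. The Consent section describes the care of patients who decline, not the contents of the database. It makes propofol with alfentanil the more likely source but does not establish it. A reader might infer that the target is 580 to 493 mg against an alfentanil control; the article does not go that far. The 57.5% is unaffected, because it uses only the 20–50% and the 15% as worded.

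On dropout, the gap is 2 patients per group, or 4 against 170 (2.4%). The 10% is itself a planning guess, and 15.1% is still about 15%. Starting from the normal-approximation figure, 75/0.90 = 83.3 lies close to 83. That route begins from 75 where the plan states 76, and it rounds up to 84. The objection nevertheless removes any claim of material consequence.

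**Conclusion.** The 65% is wrong on the bases the article itself states; the maximum is 57.5%. The conclusion rests on reading the 15% as relative to the alfentanil regimen, which is how the sentence is worded. It is a minor error of 7.5 percentage points in the supporting argument.

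A reader might infer that the sample size is wrong or the trial underpowered. The article does not support that: 76 per group reproduces from its own inputs, and the 65% plays no part in it. Nor does the correction overturn the case for clinical relevance.

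The dropout figure is a rounding matter. The arithmetic calls for 85 per group, but with 83 the cost at 10% loss is about 0.6 of a percentage point of power (0.794 against 0.80), or 1 point if the evaluable number is taken as 74.

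**What to change.** 1. Replace the 65% with a maximum of about 57.5% relative to propofol alone. If percentage points of the propofol-alone dose were meant, say so and reconcile that with the 15% of 580 mg used for sizing.
2. State which sedation regimen the 580 mg database mean reflects.
3. Restate the allowance for loss: 166 randomized patients keep 76 evaluable per group with up to 8.4% loss, and with 10% loss power is about 79%.

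The cost is a few reworded sentences and slightly less favourable figures. Enrolment, endpoint and analysis do not change.
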